#### Secondary outcome

The secondary outcome is change in the sensory evaluation of the intervention foods. The secondary endpoint is changes in the sensory parameters for liking of the intervention food prepared as meals.

The hypothesis is that the liking and acceptance of the novel products will increase over time [27, 41, 42]. Demographic and anthropometric measures, as well as other individual-level characteristics (degree of food neophobia and food disgust, earlier exposure to edible insects), are included as explanatory variables.

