## Materials and methods

### Study design

The study is a two-arm randomized equivalence intervention trial. The participants are recruited from families. In each family, one adult and one 8–10 year-old child are enrolled as paired participants. The families are provided products incorporating alternative proteins (insect-based or plant-based) suited to replace meat in dinner meals three times per week, for 6 weeks.

Figure 1 depicts the study flowchart. Recruitment, information meetings, collection of informed consent, and other relevant duties are conducted by the on-site project management team and supervised by the PI. During the recruitment period, interested parents and children will attend an information meeting at the Department of Nutrition, Exercise and Sports of the University of Copenhagen, formally enrolling to participate when signing consent. Subsequently, participants receive instructions for baseline measurements. Baseline measurements are completed during the following week, to estimate habitual protein intake (urine and dietary registrations), food neophobia (questionnaire), food disgust (questionnaire), and previous exposure to edible insects (questionnaire). Participating adults will complete a household characteristics questionnaire and a meat attachment questionnaire. One week later, the participants are returning to the department for random allocation to experimental diets, and distribution of products for the following 2 weeks. During that visit, anthropometric measurements will be collected prior to the start of the dietary intervention. Daily food records (questionnaire) will start during the first week of the dietary intervention up to the final day of the dietary intervention. Intervention week 1 includes the baseline food acceptability and feedback questionnaire, to be completed by the participating adult and child. Intervention week 5 includes the endline food acceptability and feedback questionnaire. During intervention week 6, the paired participants will collect endline urine samples and complete the endline 4-day dietary registrations and end-of-study questionnaires. To aid with retention, reminders are sent to participants to complete the registrations, questionnaire, and prior to appointments.

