### Intervention menu

Three study food products will be delivered per week over the 6-week study period. One of two menus (insect-based or plant-based) will be assigned to the paired participants. A randomly assigned sub-menu (a, b, or c) will determine the order of foods throughout the study. During the first 2 weeks of the study, participants will try each of the six selected food products from their assigned menu. In the following weeks, the assigned sub-menus will provide the same number of meals for each of the food products, with only the assigned order differing between the sub-groups.

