#### Exposure to edible insects

A modified exposure questionnaire adapted from Verbeke [28] is specific to insect-based foods but will be administered to all participants prior to randomization. Participating adults and children will select the statement that best applies to them. The original item “I eat insects seasonally” was changed to “I’ve tried edible insects many times” to better suit the Danish population.

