### Statistics

In order to measure the 20% replacement of meat in meals with insect- or plant- based alternatives from *x̄* = 14 meals/week to *x̄* = 11.2 meals/week, we will need a sample size of 78 paired participants. This sample size is based on *α* = 0.05, *β* = 0.80, and an assumed *σ* = 7. The standard deviation of the protein intake in the target population is uncertain and the statistical power is therefore based on assumptions. The results of the study will have important scientific value independent of the assumption of statistical power.

Statistical analysis will be used to determine changes in meal patterns as counts of meals with meat and the total protein intake at baseline and endline both within and between the insect and plant groups, hypothesizing no change in total protein intake and 20% replacement of the meat meal using linear models. The same analysis will be conducted both within and between the meat proteins with the insect-based foods at baseline and endline. A Spearman’s rho test will be used to assess perception change (neophobia, exposure, and disgust) before and after the intervention. A paired sample *t*-test (or Wilcoxon test, if not normally distributed) will be used to analyze pre- and post- intervention urine samples.

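### Statistics treats exposure to edible insects as a perception that may change, but it is a pre-randomisation history item, and any later answer would largely reflect the assigned menu

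*Protocol article*

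**What the plan says.** Statistics names Spearman's rho as the method for "perception change (neophobia, exposure, and disgust) before and after the intervention". Exposure thus stands beside two attitude scales as something whose change is assessed.

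Three other places in the protocol article give it a different character:

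- **Exposure to edible insects.** The questionnaire "is specific to insect-based foods but will be administered to all participants prior to randomization". Participants choose the statement that fits them. The one response option shown contains the words "tried edible insects many times".
- **Study design.** The baseline week includes "previous exposure to edible insects (questionnaire"), named as a past event.
- **Secondary outcome.** In the list of individual characteristics, "earlier exposure to edible insects), are included as explanatory variables".

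On what the trial supplies, Intervention menu says "Three study food products will be delivered per week over the 6-week study period", and Study design says products are provided "three times per week, for 6 weeks". Objective and hypothesis identifies the insect menu as the experimental exposure and the plant menu as the positive control.

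**The concern.** A questionnaire about eating history does not measure a perception. It also records the very thing that the insect menu delivers. An insect-arm participant who eats the products has more experience of eating insects at the end than at the start, whatever has happened to their attitudes. A plant-arm participant gains none from the trial. A before-after analysis of this item therefore mostly describes who was given insects and who ate them.

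What is at stake is interpretation. Reported under the label of perception change, next to neophobia and disgust, a shift in exposure could be taken as evidence that attitudes moved. The Discussion presents psychosocial measurements as part of what the trial explores, so these results are likely to be reported.

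**Working it through.** The plan states no figure for this analysis, so there is nothing to reproduce. The check sets the sections side by side and then gives an illustration under stated assumptions.

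**1. Role of the item.** Statistics: outcome, before and after. Exposure to edible insects: history item, before randomisation. Study design: previous exposure, baseline week. Secondary outcome: explanatory variable. The last three agree with one another; Statistics does not agree with them.

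**2. What the trial adds to the history.** Insect arm: 3 occasions per week x 6 weeks = 18 at most. Plant arm: 0 from the trial.

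**3. Two cases.**
- *Not asked again.* There is no after-value, and the stated before-after analysis cannot be run on exposure.
- *Asked again.* The after-value in the insect arm depends mainly on assignment and intake.

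Both cases lead to the same edit.

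**4. Illustration of the second case.** These inputs are assumptions, not in the article:
- a three-level ordered item (never / once or a few times / many times);
- 40 independent people per arm (the randomisation list has 80 numbers, one per pair, so about 40 pairs per arm);
- 50%, 70% or 90% answering *never* at baseline, the rest split 80:20 between the middle and top levels;
- 70%, 90% or 100% of the insect arm ending in the top level;
- no insects eaten outside the trial in the plant arm.

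Expected share of the insect arm changing level = uptake x (1 - baseline share already in the top level).
- Lowest: top share 0.5 x 0.2 = 0.10, so 0.7 x 0.90 = 0.63.
- Highest: top share 0.1 x 0.2 = 0.02, so 1.0 x 0.98 = 0.98.

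A simulation of 1,000 runs per scenario gave the same range:

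| | Insect arm | Plant arm |
|---|---|---|
| Share changing level | 63% to 98% | 0% |
| Wilcoxon paired test rejects at 5% | 100% of runs | 0% of runs |
| Before-after Spearman's rho, uptake 100% | undefined in every run | 1.0 where defined |
| Before-after Spearman's rho, uptake 70% to 90% | mean 0.03 to 0.18 where defined | 1.0 where defined |

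Rho is undefined at full uptake because every after-value is the same and a constant has no rank variation. In the remaining insect-arm scenarios it was undefined in at most 3.3% of runs.

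**5. Reading.** Rho near zero in one arm and 1.0 in the other says nothing about attitude; it separates the arm that was given insects from the arm that was not. A paired test puts the same fact in the form of a small p-value. Changing the test does not remove the problem.

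**The case against.** The strongest reply is that the endline measurement is inferred. The article places the exposure questionnaire before randomisation only, and the end-of-study questionnaire is said to cover attitudes and feedback. Nothing describes a repeat item or says whether trial meals would count in it. This stands, with one qualification: Study design names the neophobia and disgust questionnaires only at baseline too, and an article may condense its schedule. The missing endline description is therefore not itself the fault. The fault is the role that Statistics gives to exposure.

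A reader might go further and infer that the result is fixed by allocation and significant by construction. If everyone who changes moves upward, a two-sided sign test gives 2 x 0.5^6 = 0.031 with only six movers. The documents do not support that reading:

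- Statistics names Spearman's rho here, not a sign or Wilcoxon test. Wilcoxon appears only as the fallback for the urine samples.
- Only one response option is shown. The number and order of the others are unknown, so a uniformly upward shift is an assumption.
- Someone already in the top category cannot move up, and the Withdrawal section foresees non-compliance. *Largely determined* is accurate; *fixed* is not.
- Adult and child share a menu, so the people in an arm are not independent movers.

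A reader might also infer a guaranteed difference between arms. Statistics specifies comparisons within and between groups for meal counts and total protein, but for perception only before and after.

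Finally, the sponsor may have meant to correlate baseline exposure with change in neophobia and disgust. That would be sensible, but the sentence does not say it and would need rewriting to do so.

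**Conclusion.** The point holds as an inconsistency with a practical consequence. Statistics assigns exposure a role that conflicts with Secondary outcome, Study design and the description of the questionnaire, and that role cannot yield an interpretable result. Either there is no after-value, or the after-value in the insect arm mainly reflects the menu and its intake.

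The size cannot be fixed from the article. The 63% to 98% changing level and the rejection in every run rest on the assumed baseline exposure, uptake and three-level scale, and the rejection rate also on a test that the protocol does not name for this analysis.

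The importance is moderate. Change in exposure is neither a primary nor a named secondary endpoint, and neither the hypothesis nor the sample size depends on it. The correction is worth making because it is simple and avoids a misleading result.

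**What to change.** In Statistics, remove exposure from the list of perceptions assessed before and after the intervention, leaving neophobia and disgust. State that the pre-randomisation exposure answer is used as an explanatory variable, or as an effect modifier for liking, neophobia and disgust, in line with Secondary outcome. If the item is asked again at endline, report it only as a check on intake of the menu, and say whether trial meals count in the answer.

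The cost is one word removed and one sentence added. No data are lost and no visit or questionnaire changes. The use of a correlation coefficient to assess change in neophobia and disgust is a separate matter that this edit does not settle.

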### Risks, side effects, and drawbacks

Participating in a study can cause some inconvenience to daily life and can be time-consuming. There are no substantial risks associated with participation in the intervention. There is no anticipated harm and compensation for trial participation.

#### Safety of study foods

The study food products are processed, packaged, and stored by the EU partners in the SUSINCHAIN project. All products are produced in Europe. The products are processed, packed and stored in locations with facilities approved by relevant national food authorities. Samples of the insect-based foods are sent to a certified laboratory for microbial tests following general food standards.

#### Safety of study procedures

Spot urine collection is non-invasive and poses no risks to the participant.

### Ethical aspects

#### Informed consent

Informed consent will include information on the study activities and procedures, right to withdrawal, collection and storage procedures, and data processing. The participating adult will sign on their own behalf and will be responsible for their own participation. The custody holders must be legally able to give written consent for the child’s participation and will be responsible for their child’s participation in the study and consent forms. Children will not be allowed to participate in the study without legal consent from their custody holders. In case of shared custody, both custody holders need to sign the informed consent, unless a power of attorney has been signed. The informed consent form is available from the corresponding author upon reasonable request.

#### Withdrawal

The participating adult as well as the custody holders can withdraw their consent for participation at any time without giving explanations and without any consequences for them or the child. If one member in the household withdraws, the other member may still participate. Both consent forms must be canceled individually.

The participants may be withdrawn at any point of the study if advised by the clinically responsible physician. The participating child may be withdrawn if it becomes evident that the child does not wish to be part of the study. Participants may be withdrawn from the study for non-compliance.

## Discussion

The results of this study contribute to the growing interest in promoting the inclusion of alternative proteins in the everyday diet. Improved insect acceptability through one-time or short exposures, such as information sessions, are documented [26, 29], but the effects of long-term exposure on reducing meat consumption remains unclear. To our knowledge, this is the longest insect protein intervention study to date that not only explores psychosocial measurements but delves into the potential of meat replacement.

This study presents several strengths. First, the study includes adult and child participants, which will highlight the differentiating perspectives that exist between age groups. Second, the products are catered to dinner meal options and surpass the scope of snack or novelty items. Third, the study is designed to directly compare with plant-based dietary intervention. Additionally, a similarly designed parallel study in Portugal is being undertaken for comparing across European populations. Limitations of the study include a limited number of participants.

## Trial status

The study protocol (version 2.0, 01 June 2022) was reformatted for submission for publication in scientific journal after receiving ethical clearance in June 2022. In case a change to the protocol is needed, an amendment application will be sent to the Danish National Committee on Health Research Ethics for review and approval. Recruitment began in August 2022 and is ongoing with an expected completion date of July 2023. Due to time allocation for implementing the study, our submission of the manuscript was the earliest possible. The results will be disseminated to interested persons through open-access publications, the SUSINCHAIN, and project website and their associated social media accounts.

## Data Availability

Any data required to support the protocol can be supplied on request. The full protocol for the current study are available from the corresponding author on reasonable request.

## Abbreviations

SUSINCHAIN: Sustainable Insect Chain
EFSA: European Food Safety Authority
GDPR: General Data Protection Regulation
